## Methods

The study is a two-arm, pilot RCT with 1:1 randomization of 60 AA participants. Blinded assessments are made at baseline (immediate post-randomization), 2.5 months, and 6.5 months (follow-up). Two booster sessions are delivered via tablet-based videoconferencing at 3 months and 5 months to stimulate ongoing use of the tablet device with access to intervention materials via videoconferencing slides and the web-based portal.

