### Content of individual intervention sessions

Intervention sessions comprise a multimedia collection of communication tools including (1) interactive videoconferencing segments to deliver education and skills training, (2) supplemental videoconferencing slides, and (3) a whiteboard that provides visual aids aligned with educational materials. Presentations incorporate the participant’s CVD risk factor data and their 10-year CVD risk based on Framingham Risk Score (FRS) [45] estimates, according to seven factors (age, gender, total cholesterol (TC), high-density lipoprotein cholesterol (HDL-C), systolic BP, anti-hypertensive medication use, and smoking status).

#### Session 1

Session 1 is designed to be a face-to-face encounter with the NHE to review study goals and the schedule of study sessions, obtain participant contact information (primary and alternate telephone numbers), establish a schedule for follow-up calls, and receive study materials. For the intervention group, subsequent sessions comprise education and skills training (15 minutes of content delivery followed by 15 minutes of skills training) for interactive learning. The comparator group receives usual care provided by their primary care physician.

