### Study outcomes

The primary outcome is behavioral self-management including physical activity, diet, medication adherence, and self-monitoring. The secondary outcomes are clinical measures for glycemic (HbA1c), BP, and lipid control (LDL-C); CVD risk assessed by Framingham Risk Score (FRS) [45]; and quality of life assessed by Medical Outcomes Study (MOS) Short Form (SF-12) [49]. Each outcome was measured at baseline, 2.5 months (immediate post-intervention) and 6.5 months for follow-up (post-randomization).

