### Sample size determination and power analysis

Pilot studies are generally not sufficiently powered to detect statistically significant effect sizes [50]; however, small differences in primary outcome results can offer a signal of benefit and will be necessary justification that it is worth testing in a subsequent larger, adequately powered trial.

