### Data analysis

#### Primary hypotheses

Compared to high-risk, low-income AAs with diabetes receiving UC, individuals randomized to the multi-component TABLETS intervention will have greater improvement in behavioral outcomes at the 6.5 months follow-up.

The intent-to-treat (ITT) sample, comprising all randomized participants, is used for primary analyses. A two-tiered analysis strategy is used for the primary and secondary aims (comparing efficacy of the TABLETS intervention compared to UC on improving the primary and secondary outcomes among high-risk AA adults). First, each primary outcome (physical activity, diet, medication adherence) and each secondary outcome (HbA1c, BP, LDL, Framingham Risk Score) is assessed separately over the 6-month study time trajectory using longitudinal data methods (generalized linear mixed effects modeling, GLMM) to compare the longitudinal trajectory of the outcomes for the two intervention groups. GLMM can accommodate different distributional assumptions for outcome variables (for example, continuous, dichotomous, or ordinal outcomes) [51] and missing data [52]. In further secondary multivariable analyses, additional covariables will be added to the model to adjust for putative confounding variables, if appropriate. Candidate covariables include, for example, age, gender, and education. Least squares means will be compared at relevant time points (2.5 and 6.5 months) using appropriate model contrasts. Second, the global benefit of the intervention based on multiple primary outcomes (physical activity, diet, medication adherence) and secondary outcomes (HbA1c, BP, LDL-C, Framingham Risk Score) will be assessed using a global statistical test (GST) [51].

An important role of a pilot study is to evaluate issues related to feasibility. Intervention feasibility measures include recruitment, compliance, and dropout proportions. For the intervention group, 95 % confidence intervals for proportions will be used to estimate the proportion of those enrolled versus those eligible, the proportion of adherers to the intervention protocol, and the proportion of drop-outs. We will describe patients’ reasons for refusing to participate and reasons for dropping out to get a better understanding of the barriers to recruitment and to implementation, respectively. Dropout proportions between the TABLETS and UC groups will be compared using logistic regression analyses.

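### The global test pools three behavioural outcomes with four clinical ones and leaves out self-monitoring, so no single test addresses the primary behavioural hypothesis as a whole

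*Protocol article*

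**What the plan says.** Under Data analysis, Primary hypotheses, the protocol article states one hypothesis: participants given TABLETS "will have greater improvement in behavioral outcomes at the 6.5 months follow-up" compared with usual care. Study outcomes defines the primary outcome with four components: "The primary outcome is behavioral self-management including physical activity, diet, medication adherence, and self-monitoring".

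Two tiers of analysis follow, serving the primary and secondary aims together.

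- **Tier 1.** Each listed outcome "is assessed separately over the 6-month study time trajectory using longitudinal data methods". The primary list holds physical activity, diet and medication adherence; the secondary list holds HbA1c, BP, LDL and the Framingham Risk Score (FRS). "Least squares means will be compared at relevant time points (2.5 and 6.5 months) using appropriate model contrasts".
- **Tier 2.** The intervention's global benefit is judged on several measures together, with the primary ones named first: "outcomes (physical activity, diet, medication adherence) and secondary outcomes (HbA1c, BP, LDL-C, Framingham Risk Score) will be assessed using a global statistical test (GST").

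Self-monitoring appears in neither tier. Content of individual intervention sessions says the FRS is computed "according to seven factors (age, gender, total cholesterol (TC), high-density lipoprotein cholesterol (HDL-C), systolic BP, anti-hypertensive medication use, and smoking status"). Sample size determination and power analysis says that "small differences in primary outcome results can offer a signal of benefit" and would help justify a larger trial.

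**The concern.** The only test that combines outcomes does not match the hypothesis printed above it. The hypothesis is about behaviour; four of the test's seven components (57%) are clinical. Two misreadings become possible. A clinical effect without behavioural change could make the global test significant and be taken as support for the primary aim. A real behavioural effect could be diluted if the clinical measures move little.

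Self-monitoring adds a second mismatch. It is a primary outcome in the Abstract, the study aim, Tables 1 and 2 and Study outcomes, yet the analysis as written neither models it nor includes it in the global test.

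A smaller point concerns weighting. Systolic BP enters the global test directly and again through the FRS.

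The stake is the decision on a larger trial, which the protocol ties to the primary outcome results.

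**Working it through.** **Outcomes side by side**

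| Outcome | Role in Study outcomes | Tier 1 | Global test |
|---|---|---|---|
| Physical activity, diet, medication adherence | primary | yes | yes |
| Self-monitoring | primary | no | no |
| HbA1c, BP, LDL-C, FRS | secondary | yes | yes |

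**Inputs from the protocol.** 60 participants randomised 1:1, so 30 per arm. No power, effect size, correlation or significance level for efficacy is stated, so there is no figure to reproduce.

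**Assumptions.** Two-sided 5%; a global test that sums the standardised outcomes with equal weights (the article does not name the type); correlation 0.2 within a domain and 0.1 across domains, except FRS–BP 0.5 and FRS–LDL-C 0.4; no dropout.

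**Formula.** λ = Σd / [√(2/30) × √S], where d is each standardised effect, S is the sum of all entries of the correlation matrix, and √(2/30) = 0.2582. Power = Φ(λ − 1.96) + Φ(−λ − 1.96).

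**S for each test**
- Seven pooled outcomes: 7 + 2 × (3×0.2 + [4×0.2 + 0.5 + 0.4] + 12×0.1) = 7 + 2 × 3.5 = 14
- Three behaviours: 3 + 2 × 3 × 0.2 = 4.2
- Four behaviours: 4 + 2 × 6 × 0.2 = 6.4

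**Results**

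| Test | True effects | Σd | λ | Rejects |
|---|---|---|---|---|
| Pooled 7 | clinical 0.5 (FRS 0.3), behaviours 0 | 1.80 | 1.863 | 46% |
| Pooled 7 | behaviours 0.5, clinical 0 | 1.50 | 1.553 | 34% |
| Pooled 7 | behaviours 0.5, clinical 0.1 (FRS 0.05) | 1.85 | 1.915 | 48% |
| Pooled 7 | behaviours 0.5, clinical 0.35 (FRS 0.2) | 2.75 | 2.847 | 81% |
| Pooled 7 | behaviours 0.5, clinical 0.5 (FRS 0.3) | 3.30 | 3.416 | 93% |
| 3 behaviours | 0.5 each | 1.50 | 2.835 | 81% |
| 4 behaviours | 0.5 each | 2.00 | 3.062 | 86% |

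A behaviours-only test rejects 5% of the time when only clinical outcomes improve.

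**Sensitivity to correlation.** Use one common correlation r for every pair, keeping FRS–BP at 0.5 and FRS–LDL-C at 0.4. Then S = 7 + 2 × (19r + 0.9) for the pooled test and 3 + 6r for three behaviours.

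| r | S pooled | Pooled, clinical only (Σd 1.8) | Pooled, behaviours only (Σd 1.5) | 3 behaviours (Σd 1.5) |
|---|---|---|---|---|
| 0 | 8.8 | 65% | 50% | 92% |
| 0.2 | 16.4 | 41% | 30% | 81% |
| 0.4 | 24.0 | 30% | 22% | 71% |

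The size of the problem changes with r; its direction does not.

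**Extra weight on BP.** Suppose only BP improves, by 0.5 SD, carrying the FRS by 0.3 SD. With the FRS in the test, λ = 0.8 / (0.2582 × √14) = 0.828, which rejects 13% of the time. Without it, S = 6 + 2 × (0.6 + 0.6 + 0.9) = 10.2 and λ = 0.5 / (0.2582 × √10.2) = 0.606, which rejects 9%. The overlap raises BP's influence modestly.

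**The case against.** The strongest defence is that the global test is offered for global benefit, not named as the test of the primary hypothesis, and that a cross-domain question is legitimate. It comes second; the separate models come first and include a 6.5-month contrast for each of three behaviours. That is correct, and it limits the point. A reader might infer that no test addresses the primary hypothesis, or that the separate models are a fallback. The document supports neither. What is missing is one test for the behavioural domain as a whole.

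Other stronger readings also fail:
- *Pooling costs power.* Only sometimes. Under the main assumptions, the pooled test matches three behaviours alone once clinical effects reach about 0.35 SD (FRS 0.2), and beats them at 0.5 SD.
- *Counting BP twice inflates type I error.* It changes the weighting. A global test that allows for correlation keeps its level. The extra weight is partial, since BP is one of several FRS factors, and the listed lipids are total and HDL cholesterol, not LDL-C.
- *Error accumulates over both visits.* The hypothesis fixes 6.5 months, and multiplicity rules may sit in an analysis plan not shown. The protocol also sets no numerical threshold for a signal, so chance rates against a chosen cut-off are not its own.

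The global-test sentence could conceivably mean one test per outcome family. The singular wording points to one pooled test; if two were meant, the text should say so. The trial is also an openly underpowered pilot, which lowers the severity.

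What the defence does not answer is that the article itself fixes the components of the global test. This is a stated choice that mismatches the hypothesis, not detail left to another document. Nor does it explain the absence of self-monitoring.

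**Conclusion.** The concern holds in limited form. As naturally read, the global test does not test behavioural improvement at 6.5 months, because a significant result may come from behaviour, clinical measures or both. The first tier covers three of the four primary behaviours one at a time; nothing covers the domain as a whole, and self-monitoring is analysed nowhere in the stated plan.

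Under the main assumptions, the pooled test rejects about 46% of the time with no behavioural effect at all (30% to 65% as the common correlation goes from 0.4 to 0). Its power for a 0.5 SD behavioural effect ranges from 34% to 93% according to what the clinical outcomes do, against a fixed 81% (three behaviours) or 86% (four). These figures rest on assumed effects, correlations, equal weights and a 5% level, and illustrate size only. The mismatch and the omission rest on the text alone. The trial remains valid; the change is a worthwhile, cheap improvement to interpretation.

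**What to change.** Revise the Data analysis wording as follows:
1. Specify one global test on physical activity, diet, medication adherence and self-monitoring at 6.5 months as the overall test of the primary hypothesis.
2. Specify a separate global test for HbA1c, BP and LDL-C, with the FRS analysed on its own.
3. Add self-monitoring to the first-tier models.
4. Keep the individual and 2.5-month contrasts as supportive estimates with confidence intervals.

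Trial status reports 92% of target recruitment and 43% with final assessments complete, so this is a mid-trial change. It should be dated, made before any unblinded analysis, and reported as a change.

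The cost is analysis wording only: Table 1 already schedules self-monitoring at baseline, 2.5 and 6.5 months. The real downside is that a benefit spread across both domains is no longer captured in one test.

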#### Qualitative data management and analysis

In the final 6.5 months assessment, those in the intervention group will be asked to participate in 30- to 40-minute, semi-structured interviews by telephone. This is an optimal time to explore participants’ perspectives, insights, needs, and preferences in their own terms [53] as they apply to intervention components (physical activity, diet, medication adherence, self-monitoring). Just as patient-physician encounters can be examined for context cues [54], research staff will use a summary of the main context cues in the four topic areas to address what worked or did not work (useful, useless components); what enabled or delayed behavior changes (facilitators, barriers); the most helpful strategies (education, motivation, skills training) to resolve challenges; and usability and satisfaction with the tablet as a self-monitoring tool. Interview methods allow flexibility to gather additional details when needed and will yield data to refine the intervention for future implementation. With IRB approval, all interviews are audio-recorded for accuracy of data and use of selected verbatim quotes. Prior to closing, key responses are summarized, and participants are asked if they have anything to add. All data will be stored on a secure server for analysis.

Inductive data analyses will be performed to examine the natural variation among the themes, patterns, and categories that emerge from semi-structured interviews. The NVivo 10 qualitative management program used for this study is designed to systematically facilitate coding, sorting, and integrating all of the data. Two coders (including the PI) will review the transcripts and apply codes (words or brief text describing context) guided by the conceptual model and intervention components in order to provide concepts used in generating the initial line-by-line codes [55]. Triggers for important words, concepts, and comments will be noted as well as their consistency among participants. The two sets of codes will then be reviewed to determine agreement (called inter-coder reliability). Differences in interpretation of codes will be discussed and resolved between study investigators. An iterative process of coding will result in a final set of codes that can subsequently be applied to transcripts to identify themes common within and across participant interviews [55]. The goal is to address important questions that have not been examined before, to “tell a story” about the participants in this study, and to conceptualize participants’ knowledge of physical activity and diet, coping and skill-building, and ability to act on self-monitored data. Findings will help refine the intervention and emphasize elements that enhance participant uptake and motivation for sustained behavior change.

## Discussion

The study was funded in September 2013. Progress has been made in identifying and building relationships with technology companies, streamlining novel information technology processes to accommodate the multimedia aspect of the intervention (tablets, videoconferencing, home monitoring devices), refinement of intervention materials, obtaining needed study equipment (such as tablet computers with the technological capacity to execute the planned intervention), and hiring and training research personnel. The overarching goal is to develop and refine intervention processes and materials that allow tablet-based delivery of education and skills training about self-management behaviors relevant to CVD risk using real-time videoconferencing among AA adults with diabetes and other CVD risk factors. Study recruitment was initiated in September 2014 with eligibility determination, randomization, and enrollment currently underway.

The proposed study provides a unique opportunity to assess the feasibility and efficacy of a theory-driven, tablet-aided behavioral intervention that utilizes real-time videoconferencing technology for education and skills training on chronic disease self-management behaviors and CVD risk among a high-risk, low-income AA population with an uncontrolled dyad or triad of CVD risk factors. In the evolution of a paradigm shift to become more person-centered in the provision of care and to drive sustainable behavior change [56], the behavioral intervention in this pilot study is adding important value to the literature on facilitating healthier self-management behaviors. The intervention will leverage the use of a novel technology for education and skill-building that fosters improved diabetes self-management in a high-risk AA population. The findings of this study, if successful, will provide the basis for disseminating the intervention to a broader and larger sample of people, and can potentially be refined to align with clinical workflows that target a subsample of patients with poor diabetes self-management.

### Trial status

At the time of submission, the study is in the final phase of recruitment and enrollment. We have completed 92 % of the target recruitment, 63 % have completed the first (2 months) follow-up visit, and 43 % have completed the second and final (6 months) follow-up assessment.

## Abbreviations

AA: African American
BP: blood pressure
CDSM: chronic disease self-management
CONSORT: Consolidated Standards of Reporting Trials
CVD: cardiovascular disease
DSM: diabetes self-management
GLMM: generalized linear mixed effects modeling
GST: global statistical test
HbA1c: glycosylated hemoglobin A1c
HIPAA: Health Insurance Portability and Accountability Act
ICD-9: International Classification of Diseases, 9^th^ revision
IMB: Information, Motivation, and Behavioral Model
IRB: Institutional Review Board
ITT: intent to treat
LDL-C: low-density lipoprotein cholesterol
NHE: nurse health educator
NIDDK: National Institute of Diabetes and Digestive and Kidney Diseases
PCP: primary care provider
PI: principal investigator
RA: research assistant
RCT: randomized controlled trial
SC: South Carolina
SD: standard deviation
T2DM: type 2 diabetes mellitus
TABLETS: Tablet-Aided BehavioraL intervention EffecT on Self-management skills
UC: usual care
